#### Data collection and linkage

Children referred to children’s services in applicable English local authorities (FGC providers and non-providers) during the intervention period (2017–19) will be identified from the Child in Need dataset within the National Pupil Database (NPD, Department for Education) which can be used to identify all school-aged children. This period has been selected on the basis of this being the most recent available where two-year follow-up in routine data is possible. The unique pupil ID can be used to link to other relevant NPD datasets, including Child Looked After, school attendance and special educational needs. Matching to Hospital Episode Statistics (HES) records will be undertaken using standard linkage strategies for HES and NPD data (e.g., using date of birth, gender, postcode) and quality of linkage assessed by estimating rates and distribution of linkage errors. Linkage will be achieved via the E-CHILD database [42]. Identifiers for FGC families will be supplied by local authorities. Health care records for birth mothers will also be matched in E-CHILD. The exact model for data linkage will be established in WP1. Anonymised, linked data will be accessed via the ONS Secure Research Service (ONS-SRS) and analysed by Cardiff and Oxford University staff via verified remote access.

We will follow up children in these datasets for two years following the date of referral. We have allowed for this work package to run throughout the four years of the project in recognition that permissions for data linkage and the delivery of linked data are very time consuming and often subject to delays. We also need to allow for follow-up. The latest follow-up data will be recorded in December 2021 and this data set will be first available to researchers in the Spring of 2023, two years into the project.

The Covid-19 lockdowns will influence the patterns of service provision from the end of March 2020, but this will be the same for families who have and have not taken part in an FGC between 2017 and 2019 and changes in service patterns will be interesting in their own right. Any difference between FGC and non-FGC families in post-lockdown trends can be noted. How Covid-19 and lockdowns affect the data will be considered when we write a definitive analysis plan.

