### Work Package 3: Comparison of service use and associated costs in FGC participants and a comparison group after two years using a quasi-experiment (RQ4)

Public-facing title: Service use study (Family VOICE project)

WP3 is a quasi-experiment to assess service use outcomes of FGCs and the economic dimension of these. The experimental dimension is comparison of families who have had FGCs with similar families in local authorities with no FGC provision. This work package will assess some longer-term outcomes from the programme theory developed in WP1 for which administrative data are more suitable than self-report, because of the need for complete coverage of the relevant population without social desirability bias.

Outcomes to be measured include:

1. Primary outcome

The primary outcome is whether category (of seriousness) of children’s social care intervention at two years after FGC (or equivalent date for comparison group) is the same level, lower or higher than at the time of FGC. A ladder of escalation will be used, with state intervention categories ordered from most to least serious, including the child having been:

categorised as in need (and reason for this);subject to a child protection investigation;on a child protection plan;looked after by the local authority (and, if so, on what legal basis; type of care–foster, kinship, residential, placed with parents).

The primary outcome variable will be binary, describing whether the category of statutory intervention at 2 years after FGC (or equivalent date for the non-FGC group) is the same or lower than at the time of FGC (or equivalent date) or whether it is higher.

2. Secondary outcomes

Highest category of children’s social care intervention since the FGC (or equivalent date for comparison group) at any time during the two-year follow-up.

A summary measure of duration and seriousness of all children’s social care intervention during follow-up.

Health care use for health conditions and events which might potentially be affected by FGC attendance–e.g., child and parent mental health, serious injury to a child, assault resulting from domestic abuse:

hospital admissions;outpatient appointments;‘Improving Access to Psychological Therapies’ [39] services;community mental health services;accident and emergency attendances.

Absence from school and special educational needs provision.

Incremental cost per adverse social-care-outcome-adjusted year avoided.

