#### Sampling, settings and research participants

Families who have attended FGCs will be identified by local authorities–we will work with several large authorities in England, and access anonymised data from the Department for Education, NHS Digital and the Office for National Statistics (ONS). This part of the study is not linked in any way to the WP2 families. In these participating local authorities, we will also access routine data on families who have been referred to children’s services but have not had an FGC, in order to delineate the circumstances in which families do and do not take part in FGCs in these particular authorities.

A comparison group of local authorities which do not offer FGCs will be identified in the WP1 survey. Families from these authorities will be identified from the Children in Need Census. This part of the study uses data from only one UK country–England–because the datasets are different for each nation and given the complexity of data linkage it would not be feasible to attempt this study in more than one nation. We have chosen England as having the largest population.

Eligible families will be those with at least one child under 18 years of age referred to departments of Children’s Social Care Services from 1.1.17 to 31.12.19 at participating local authority sites in England (there is no intention to connect these local authorities to those taking part in earlier work packages). No additional exclusion criteria will be applied. At this stage we are not imposing a lower age limit. However, although we are confident that linkage to health records for school-age children is viable, there is some uncertainty about this linkage for pre-school children. We will therefore have to test the feasibility of extending the age profile to include all children from birth, in the early stages of WP3.

To make the two groups of families from different local authorities comparable for analysis, we will use statistical techniques to improve balance across the two groups for several known confounders. We will use propensity score weighting [40, 41] to estimate the average ‘causal’ effect of having an FGC on the outcomes.

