#### Data analysis

We will use Stata or R software to estimate a family’s propensity for having an FGC with a logistic regression on variables including stage of the child welfare process (referral, child in need, child protection assessment, child protection plan), reason for referral and family demographics. The analysis model for the primary outcome variable (whether the level of social care intervention at two years after the FGC–or equivalent baseline date for the control group–has increased or not) will be two-level logistic regression, with random effects for local authorities and weighting of families according to their propensity for having an FGC. Fixed effects will include intervention (whether a family has had an FGC or not) as well as other factors–to be determined in WP1 –to account for the different ways FGCs are set up in different local authorities. Effect estimates will be presented with two-sided 95% confidence intervals and p-values. Secondary outcomes will be analysed using the same propensity score weighting approach and appropriate two-level regression models depending on the type of outcome variable (e.g., logistic for binary outcomes, linear for continuous outcomes).

We will undertake multiple imputation to explore the impact of potential missing data. We will also consider alternative covariate balancing or matching methods, such as entropy balancing [43], Mahalanobis distance matching [44] and coarsened exact matching [45] if propensity score weighting does not achieve good enough covariate balance and/or as sensitivity analyses. Detailed statistical analysis plans for WP2 and WP3 will be finalised prior to any analysis being performed, and these will be published on the study website.

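### WP3 counts its two years from the FGC in the outcome definition but from referral in the follow-up rule, and the eligibility window and data end leave no room for the gap between the two

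*Protocol article*

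**What the plan says.** Three parts of Work Package 3 in the protocol article bear on the time origin.

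- **Outcome definition** (Work Package 3, primary outcome). The binary outcome is "whether the category of statutory intervention at 2 years after FGC (or equivalent date for the non-FGC group) is the same or lower" than it was at the FGC, or whether it is higher. The Data analysis section repeats this anchor, describing "whether the level of social care intervention at two years after the FGC", with an equivalent baseline date for the control group. Both baseline and endpoint are therefore tied to the FGC.
- **Follow-up rule** (Data collection and linkage): "We will follow up children in these datasets for two years following the date of referral". The same paragraph identifies children by referral to children's services, in FGC-providing and non-providing authorities alike. Referral here cannot mean referral to an FGC.
- **Window and data end.** Sampling, settings and research participants admits families referred "from 1.1.17 to 31.12.19 at participating local authority sites in England" and applies no further exclusions. Data collection and linkage adds: "The latest follow-up data will be recorded in December 2021".

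The only text that places the FGC itself in calendar time is indirect. The Covid-19 paragraph says of lockdown effects that "this will be the same for families who have and have not taken part in an FGC between 2017 and 2019". The data collection section also calls 2017 to 2019 the intervention period, and the WP1 survey calls it the baseline period for WP3. None of these is written as an eligibility rule.

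**The concern.** The two rules agree only if the FGC takes place on the day of referral. The article indicates that this is not the usual case. Its stage variable runs from referral through to a child protection plan, and its examples of FGC contexts include edge of care and the pre-proceedings stage, which families reach some time after referral.

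What is at stake is whether the primary outcome can be computed as defined. A data request or analysis file built on the follow-up rule stops short of the endpoint that the outcome definition requires. One built on the outcome definition runs past the end of the data for late FGCs. The secondary outcome on the highest category since the FGC and the two-year cost comparison depend on the same window.

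**Working it through.** **The plan's own figure.** The article gives a detectable difference of 10.5 points with 300 and 1000 families, 90% power, two-sided 5%, proportions near 0.5. The simple formula gives (1.960 + 1.282) × √[0.25 × (1/300 + 1/1000)] = 0.107. The pooled-variance two-sample test gives 10.6 points at 90% power, and its power at 10.5 points is 89.2% (0.4475 v 0.5525) to 89.7% (0.50 v 0.605). The figure reproduces and is not in dispute.

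**Calendar.** The last eligible referral is 31.12.2019. Adding 24 months gives 31.12.2021, and the last data are from December 2021. There is no slack.

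**Inputs for the size.** The referral window is 36 months (article). The referral-to-FGC lag L is not given and is shown here as an assumed range. Referrals are assumed uniform over the window, with a fixed lag.

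- Two years counted from referral: post-FGC follow-up = 24 − L months.
- Two years counted from the FGC: share of FGC families with an FGC after December 2019, and so no two-year value = L/36.
- Power if those families are lost and not replaced: n₁ = 300 × (1 − L/36), n₂ = 1000, proportions 0.4475 and 0.5525, pooled-variance test, before any loss from weighting.

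| Lag (months) | Post-FGC months if counted from referral | Share with no two-year value if counted from FGC | Of 300 | Power at 10.5 points | Difference detectable with 90% power |
|---|---|---|---|---|---|
| 0 | 24 | 0% | 0 | 89.2% | 10.6 |
| 1 | 23 | 2.8% | 8 | 88.6% | 10.8 |
| 3 | 21 | 8.3% | 25 | 87.2% | 11.0 |
| 6 | 18 | 16.7% | 50 | 84.6% | 11.4 |
| 12 | 12 | 33.3% | 100 | 77.6% | 12.5 |

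The fixed lag is not critical. With an exponential lag of mean m, the share is m(1 − e^(−36/m))/36, which gives 8.3%, 16.6% and 31.7% for means of 3, 6 and 12 months.

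The two columns of consequences are alternatives. The first applies to every FGC held after referral if the follow-up rule is taken literally. The second applies only to late FGCs if the outcome definition is followed.

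**The case against.** The strongest reply is that the two sections that define and analyse the outcome agree with each other. Both anchor it at the FGC and both require an equivalent date for comparison families. How that date is derived is operational detail that a condensed article may leave to the analysis plan, which the article promises to finalise before any analysis. The late-FGC point is also partly answered: if the remarks about 2017 to 2019 describe FGC dates, an FGC on 31.12.2019 reaches two years on 31.12.2021, inside the data.

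Much of this stands, and it rules out several stronger readings that a reader might infer:

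- *That the study has no common time zero.* The outcome definition does give one, for both groups.
- *That escalation before the FGC would be counted as an FGC outcome.* The baseline category is taken at the FGC. No section states a referral baseline; the follow-up sentence shortens follow-up but does not move the baseline.
- *That FGC families start at the FGC and comparison families at referral.* This is written nowhere, and it contradicts the requirement of an equivalent date.
- *That a spurious difference of a given size follows.* Any such figure needs ladder-transition rates and a lag that the article does not give. A hypothetical model can illustrate a mechanism but cannot estimate the bias here.
- *That lockdown exposure is shown to differ between groups.* The article defers Covid-19 effects to the definitive analysis plan.

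What the reply does not remove is the contradiction. An analysis plan can define the equivalent date, but it cannot follow both the outcome definition and the follow-up sentence. The window that is written as an eligibility rule is on referral, not on the FGC.

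**Conclusion.** The concern holds as an inconsistency about when the two years start, together with an eligibility window on the wrong date for the stated outcome. Under the follow-up sentence, the primary outcome as defined is not observed for any FGC held after referral. Under the outcome definition, it is missing for FGCs held after December 2019 unless the 2017 to 2019 remark becomes a rule.

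The existence of the conflict rests on the text alone. Its size rests on an unstated lag: roughly 3% to 33% of FGC families for lags of 1 to 12 months, assuming uniform referrals. The power figures hold only if the lost families are not made up; the abstract gives 300 as a minimum, so they might be. Neither a direction nor a size of bias in the primary comparison is established.

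**What to change.** 1. In Data collection and linkage, replace the follow-up sentence so that each child is followed for two years from the FGC date or, for a comparison family, from its equivalent date.
2. In Sampling, settings and research participants, add that the FGC or equivalent date must fall between 1.1.17 and 31.12.19. Every two-year date then falls by 31.12.21.
3. State that the baseline category and the propensity covariates are measured on that same date in both groups.
4. State that the comparison family's date lies at a comparable point after referral and not at referral itself. One workable way is to draw it from the observed referral-to-FGC lag, among cases still open on that date; other methods that achieve the same alignment would serve.

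The cost is a few sentences and some programming. FGCs held after 2019 are dropped: under the assumptions above, the same L/36 share, but by a stated rule applied to both groups and not as missing outcomes in one. If later data can be obtained, a later data end would keep them.

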#### Data analysis

We will use Stata or R software to estimate a family’s propensity for having an FGC with a logistic regression on variables including stage of the child welfare process (referral, child in need, child protection assessment, child protection plan), reason for referral and family demographics. The analysis model for the primary outcome variable (whether the level of social care intervention at two years after the FGC–or equivalent baseline date for the control group–has increased or not) will be two-level logistic regression, with random effects for local authorities and weighting of families according to their propensity for having an FGC. Fixed effects will include intervention (whether a family has had an FGC or not) as well as other factors–to be determined in WP1 –to account for the different ways FGCs are set up in different local authorities. Effect estimates will be presented with two-sided 95% confidence intervals and p-values. Secondary outcomes will be analysed using the same propensity score weighting approach and appropriate two-level regression models depending on the type of outcome variable (e.g., logistic for binary outcomes, linear for continuous outcomes).

We will undertake multiple imputation to explore the impact of potential missing data. We will also consider alternative covariate balancing or matching methods, such as entropy balancing [43], Mahalanobis distance matching [44] and coarsened exact matching [45] if propensity score weighting does not achieve good enough covariate balance and/or as sensitivity analyses. Detailed statistical analysis plans for WP2 and WP3 will be finalised prior to any analysis being performed, and these will be published on the study website.

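### WP3 adjusts for the baseline intervention category, from which the primary outcome is defined, only through the propensity weights, so the stated analysis is not doubly robust and is exposed if the top rung is handled badly

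*Protocol article*

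**What the plan says.** **Outcome.** The Work Package 3 section of the protocol article sets out a ladder of statutory intervention and derives the primary outcome from it: "The primary outcome variable will be binary, describing whether the category of statutory intervention at 2 years after FGC" is higher than at the time of the FGC (or equivalent date), as opposed to the same or lower. The most serious category listed is "looked after by the local authority (and, if so, on what legal basis". The first secondary outcome is "Highest category of children’s social care intervention since the FGC (or equivalent date for comparison group) at any time during the two-year follow-up".

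**Propensity model.** The Data analysis section for Work Package 3 fits a logistic model whose predictors are given as: "variables including stage of the child welfare process (referral, child in need, child protection assessment, child protection plan), reason for referral and family demographics".

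**Outcome model.** The same section plans two-level logistic regression "with random effects for local authorities and weighting of families according to their propensity for having an FGC". On covariates it says "Fixed effects will include intervention (whether a family has had an FGC or not) as well as other factors", and gives the purpose of those other factors as "to account for the different ways FGCs are set up in different local authorities". Secondary outcomes use the same weighting approach.

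**Fallback.** Entropy balancing, Mahalanobis distance matching and coarsened exact matching will be considered "if propensity score weighting does not achieve good enough covariate balance and/or as sensitivity analyses".

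**The concern.** An outcome defined as movement up from a starting rung depends on that rung, because it decides how many rungs are left to climb. A child already looked after has no higher main category to reach. The highest category during follow-up is tied to the starting rung just as closely.

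The starting category will be available, since the outcome cannot be computed without it. Yet in the stated analysis it enters only through the weights. If the propensity model is right, that is enough to remove confounding by baseline. If it is wrong about baseline, nothing in the stated outcome model makes up for it.

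The risk is practical because the two lists of categories do not match. The propensity stages run from referral to child protection plan; the outcome ladder runs up to looked after. The propensity list is introduced as including these variables, so the missing rung is not excluded. But the rung not named is the one whose children cannot escalate.

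**Working it through.** **1. The plan's own figure.** Inputs from the Work Package 3 sampling section: 300 FGC families, 1000 controls, proportions around 0.5, 90% power, two-sided 5%. With the variance fixed at 0.25, SE = sqrt(0.25 × (1/300 + 1/1000)) = 0.0329, and the detectable difference is (1.960 + 1.282) × 0.0329 = 0.107. For 0.5 against 0.605 the power is 0.897. The stated 10.5 points is reproduced. It assumes no covariate adjustment.

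**2. Assumptions.** The protocol gives neither the category mix nor escalation risks by category, so these are illustrative. Rungs run from lowest to highest.

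| | 1 | 2 | 3 | CP plan | Looked after |
|---|---|---|---|---|---|
| FGC share | 0.10 | 0.20 | 0.20 | 0.35 | 0.15 |
| Control share | 0.30 | 0.30 | 0.15 | 0.15 | 0.10 |
| Risk, strong | 0.75 | 0.60 | 0.45 | 0.25 | 0 |
| Risk, moderate | 0.50 | 0.45 | 0.40 | 0.25 | 0 |
| Risk, weak | 0.30 | 0.28 | 0.26 | 0.24 | 0.20 |

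The true effect is zero unless stated. Weights target the FGC families (FGC weight 1, control weight e/(1 − e), where e is the propensity). There is no authority clustering.

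**3. Bias if the propensity model merges the top two rungs.** Weighting gives the merged group the FGC share, 0.35 + 0.15 = 0.50, in both arms. Within it, controls keep their own 0.15 : 0.10 split, so the weighted controls are 0.30 child protection plan and 0.20 looked after, against 0.35 and 0.15 in FGC families.

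- Strong or moderate: 0.35 × 0.25 − 0.30 × 0.25 = 0.0875 − 0.0750 = 0.0125, or 1.25 points against FGC.
- Weak: (0.35 × 0.24 + 0.15 × 0.20) − (0.30 × 0.24 + 0.20 × 0.20) = 0.114 − 0.112 = 0.2 points.

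Simulations (1,500 data sets) gave 1.40 points (strong), 1.32 (moderate) and 0.25 (weak). A further check gave results from about 1.1 points upward with a prognostic baseline. With all five rungs as fixed effects in the weighted model, the bias was 0.14, 0.08 and 0.05. With weights for the whole population it was 0.90 and 0.85 points (strong, moderate) without the term, and 0.12 and 0.08 with it.

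**4. Precision when the propensity model is correct (risk difference).** The SE here is the robust one that treats the weights as known.

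| Baseline | True SD, either model | Mean SE, weights only | Mean SE, term added |
|---|---|---|---|
| Strong (R² 0.22) | 0.0287 | 0.0331 | 0.0293 |
| Moderate (R² 0.12) | 0.0299 | 0.0316 | 0.0297 |
| Weak (R² 0.005) | 0.0303 | 0.0300 | 0.0298 |

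The true SD is the same with or without the term. Only the estimated SE changes: 0.0331/0.0287 = 1.15 in the strong case, 0.0316/0.0299 = 1.06 in the moderate case, and no excess in the weak case. Between-category variance left in the residual accounts for this: 0.0331 × sqrt(1 − 0.22) = 0.0292.

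**5. The planned log-odds scale.** In these runs (1,000 data sets) the top-rung risk was set to 0.03 (strong) and 0.05 (moderate). Under no effect, adding the term widens the SE from 0.142 to 0.161 (strong) and from 0.148 to 0.156 (moderate), because the coefficient becomes a conditional log odds ratio. With a conditional log odds ratio of −0.5, power goes from 0.80 to 0.86 (strong), 0.85 to 0.87 (moderate) and 0.83 to 0.84 (weak).

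**The case against.** **The covariate list is open and an analysis plan is to follow.** This is true: the fixed effects are described as including certain items, and nothing excludes baseline category. But the article gives a purpose for the extra factors, and that purpose is service set-up, not family baseline status. Stage, referral reason and demographics are assigned to the propensity model. The stated design is weighting-only, even though it can still be changed.

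**The plan has fallbacks.** This stands in part. A reader might infer that there is no protection if the propensity model is wrong, and the protocol does not support that. A baseline category with a handful of levels is easy to check and can be balanced exactly. But these methods act only on covariates as coded and checked. If looked after is merged with another rung, the balance table on the merged variable looks perfect.

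**Intervals and power.** A reader might infer that the confidence intervals will be too wide and that power falls below the plan's figure. Neither follows. An over-wide interval needs a prognostic baseline, a variance that treats weights as known (the protocol states no variance method) and no authority clustering. With clustering, that SE was too small in a further check. As an illustration, an intraclass correlation of 0.02 with 5 and 10 authorities adds a between-authority SD of sqrt(0.02 × 0.25 × (1/5 + 1/10)) = 0.039, larger than any SE in the table. On the planned log-odds scale the SE widens with adjustment. And since the 10.5 points assumes no adjustment, forgoing a gain is not a loss against it.

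**Weighting alone is a recognised way to estimate an average effect.** Also true. Lack of double robustness is not in itself an error; it matters here because the outcome is built from the covariate in question.

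**Conclusion.** The point holds in a limited form. As stated, the primary analysis controls baseline category through the weights alone, although the outcome is defined from that category, and the propensity stage list does not name the rung from which escalation is impossible. The analysis is therefore not doubly robust on its most obviously prognostic covariate.

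If the propensity model handles the top rung badly, the bias is about 1.1 to 1.4 percentage points with a prognostic baseline and weights targeting FGC families, against about 0.2 or less with the term. That is modest beside a 10.5-point target, but avoidable. If the propensity model is correct, the estimator's true precision is unchanged, and the power gain of about 0 to 6 points comes from an SE that no longer counts between-category variance as residual.

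All these sizes rest on an assumed category mix and assumed risks, without authority clustering, and the bias figures also on an assumed merging of two rungs that the protocol does not state. The point should be settled before the analysis plan is final; it does not undermine the study.

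**What to change.** - Add baseline category, with every rung including looked after, as a fixed effect in the weighted two-level logistic model for the primary outcome and in the model for highest category during follow-up.
- Make the propensity model and its balance checks cover the same rungs, uncombined.
- Say how children who cannot escalate are handled. A rung with no possible events has no finite logistic coefficient.
- Report a standardised (marginal) effect so that the target remains the average effect.
- Use a variance that allows for the estimated weights and for local-authority clustering.
- Keep the weighting-only model as a sensitivity analysis.

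The cost is analysis-plan wording and no new data. The one real downside is that the raw coefficient becomes a conditional odds ratio, so the standardisation step is needed.

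### The WP3 primary model adds fixed effects for how FGCs are set up, which no control family can have; unless these are centred or standardised, the intervention term need not be the average effect of having an FGC

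*Protocol article*

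**What the plan says.** The target is stated in the protocol article, Work Package 3, Sampling, settings and research participants: propensity score weighting is used "to estimate the average ‘causal’ effect of having an FGC on the outcomes".

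The comparison is stated in the introduction to Work Package 3 as "comparison of families who have had FGCs with similar families in local authorities with no FGC provision". The sampling section adds: "A comparison group of local authorities which do not offer FGCs will be identified in the WP1 survey". Families in FGC authorities who did not have an FGC are also accessed, but only to describe who does and does not take part. They are not controls.

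The primary model, in the Work Package 3 Data analysis section, is "two-level logistic regression, with random effects for local authorities and weighting of families according to their propensity for having an FGC". On its terms: "Fixed effects will include intervention (whether a family has had an FGC or not) as well as other factors". Which factors these are is left to WP1, but their purpose is given: "to account for the different ways FGCs are set up in different local authorities". The section says that effect estimates will be presented with confidence intervals and p-values. It gives no coding for control families, no centring and no standardisation step. Detailed analysis plans are to be finalised before any analysis.

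**The concern.** Set-up describes how an FGC is delivered. A family in an authority without FGCs has no value for it, so the factor is nested inside the intervention group. It cannot confound a comparison of FGC with no FGC, because it is part of what is being compared.

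Once terms of this kind sit beside the intervention indicator, the meaning of the intervention coefficient depends on how they are coded. The plan's question (RQ4) and its stated target concern having an FGC, averaged over the families who had one. A coefficient that refers to one set-up, chosen by software default or by analyst preference, answers a different question and can change size or sign with the reference level. The study's own premise, in its introduction and in RQ3, is that delivery varies and that the variation may matter, so effects that differ by set-up are not a remote possibility.

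**Working it through.** **1. The plan's own figure.** Inputs from the sampling section: 300 FGC and 1000 control families, proportions around 0.5, 90% power, 95% confidence (taken as two-sided 5%), 10.5 points detectable. A two-sample test of proportions with a 10.5-point difference has power 0.893 to 0.897, depending on where the two proportions lie around 0.5. The figure reproduces. It is for the plain FGC versus no-FGC contrast, with no set-up terms.

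**2. What the intervention coefficient means.** Let T = 1 for FGC families. Take two set-ups, A and B, with S = 1 for FGC families under B and S = 0 for everyone else, including controls.

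logit(p) = b0 + b1·T + b2·S

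- control: b0
- set-up A: b0 + b1
- set-up B: b0 + b1 + b2

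So b1 = logit(pA) − logit(pC), the effect of A against control. With B as reference, b1 = logit(pB) − logit(pC). Propensity weights and random authority effects do not remove the nesting, because set-up and FGC provision are both features of the authority.

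**3. If no FGC is its own set-up level.** The columns are intercept, T, A and B, with T = A + B. The rank is 3 with 4 columns, so the intervention term is not separately estimable.

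**4. Illustration.** The protocol gives no rates by set-up. Assumed escalation risks: control 0.30, A 0.28, B 0.20, with half the FGC families in each.

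- Odds: control 0.30/0.70 = 0.4286; A 0.28/0.72 = 0.3889; B 0.20/0.80 = 0.2500.
- FGC average risk = (0.28 + 0.20)/2 = 0.24; odds 0.24/0.76 = 0.3158.
- Intervention only: OR = 0.3158/0.4286 = 0.74.
- Set-up dummy, A as reference: 0.3889/0.4286 = 0.91.
- Set-up dummy, B as reference: 0.2500/0.4286 = 0.58.
- Set-up centred on the observed mix: √(0.9074 × 0.5833) = 0.73, whichever level is the reference.

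**5. A harsher assumption.** Control 0.40, set-ups 0.30 and 0.50, 150 families in each, 1000 controls; no clustering or weighting.

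| Model | Intervention OR |
|---|---|
| Intervention only | 1.00 |
| Dummy, first set-up as reference | 0.64 (95% CI 0.44 to 0.93, p = 0.020) |
| Dummy, second set-up as reference | 1.50 (95% CI 1.06 to 2.12, p = 0.021) |
| Centred on the observed mix | 0.98 |

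Effect coding is not a general remedy. It gives an unweighted mean over set-ups: with 100 and 200 families it returns 0.98, where the intervention-only OR is 1.15 and centring gives 1.13.

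**6. Precision with one set-up factor.** Detectable difference = 3.242 × 0.5 × √(1/m + 1/1000), where 3.242 = 1.960 + 1.282 and m is the number of FGC families that inform the coefficient.

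- m = 300: 3.242 × 0.5 × 0.0658 = 10.7 points
- m = 150: 3.242 × 0.5 × 0.0876 = 14.2 points

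**The case against.** The best defence is that little is fixed yet. The factors are deferred to WP1, and coding, centring and standardisation are ordinary content for an analysis plan that is not shown. A model with set-up terms can be valid, as the centred results show. This stands in part. A reader might infer that the protocol commits the sponsor to reporting the effect of an arbitrary reference set-up. The document does not support that: it names no reference level or coding, and does not say that one raw coefficient is the sole primary result. What the deferral does not change is that terms described as FGC set-up share the primary model with the intervention indicator, while all controls lack them. Choosing different set-up factors leaves the nesting in place.

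Second, WP1 might settle on authority characteristics that exist in both groups. The WP1 survey covers all authorities and collects contextual information. Such factors would be harmless, but the stated purpose is about how FGCs are set up, so this is not the natural reading.

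Third, the size is assumed. If effects do not vary by set-up there is no distortion, and a change of sign needs set-ups that act in opposite directions. This stands.

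Fourth, a reader might infer a certain loss of precision, or a special collinearity with the authority effects. Neither is established. The 14.2-point figure holds for a single set-up factor with no clustering; with several additive factors, other FGC families also contribute. Set-up terms could also reduce the residual variance between authorities. Authority-level fixed effects beside random authority intercepts are routine, and the intervention is itself an authority-level contrast here. The base rate matters too: at a proportion of 0.30, replacing 0.5 by √0.21 = 0.458 gives 9.8 and 13.0 points instead of 10.7 and 14.2.

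**Conclusion.** The point holds in conditional form. The primary model as described includes FGC-specific factors that are undefined for every control family, and the article gives no step that returns the intervention term to the average effect of having an FGC. The mismatch with the stated target arises if the factors really are FGC set-up factors, are entered as uncentred dummies without standardisation, and effects differ by set-up.

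Under the assumed rates, an average OR of 0.74 would then be reported as 0.91 or 0.58 according to the reference. The less favourable detectable difference is a further possible cost, not a demonstrated property of the two-level weighted model. The stated 10.5-point figure is not in error. The correction matters because it decides what the primary estimate means.

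**What to change.** In the analysis plan, leave FGC-specific set-up factors out of the primary model. Keep the intervention indicator, the propensity weights and the random authority effects, and allow as further fixed effects only authority characteristics that are defined in both groups. Study set-up in a secondary analysis restricted to FGC families.

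If set-up terms are kept in the primary model, centre them on the observed mix among FGC families, or declare the marginally standardised average FGC effect as the primary estimate. In either case do not enter no FGC as a set-up level alongside the intervention indicator.

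The cost is a sentence or two in the plan before it is finalised. No extra data are needed and the sample size statement is unchanged.
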